#### 2.8.6 Safety outcomes and adverse events

Safety assessments including vital signs, routine blood and urine tests, 12-lead electrocardiogram, and hepatic function (AST/ALT/GGT) and renal function tests will be conducted. General vital signs (body temperature, heart rate, respiration rate, and blood pressure) will be assessed at baseline and at weeks 4, 6, 8, and 12. Routine blood and urine tests will be performed at baseline and weeks 6 and 12.

An adverse event (AE) is defined as any adverse medical event that occurs between the time the participant signs the informed consent and the last follow-up visit, whether or not it is causally related to the study drug. Adverse events, such as subjective patient discomfort and abnormalities in laboratory tests will be carefully analyzed and investigated during each follow-up visit. Overall, JTTF is relatively safe and may be associated with mild diarrhea. If this occurs, consider taking half the dose for 2 days. Absence of remission or exacerbation may be reported to the Principal Investigator, unit management, and the Ethics Committee after evaluation, followed by completion of an AE reporting form. All adverse events will be followed until the condition is stable (discontinuation of observation is considered medically acceptable) or complete resolution has been achieved.

### 2.9 Randomization and data collection

Patients successfully enrolled in the study will be randomly assigned to either the treatment or control group at a 1:1 ratio. The randomization sequence number will be sealed in an opaque envelope and provided only to clinicians so that the participants can be assigned to the treatment regimen accordingly. Since this trial is an open-label study, participants and physicians will be aware of the assignment protocol, whereas data analysts and statisticians will not be aware of the distribution results.

In this study, all participants’ data will be collected, recorded, and administered in the CRF provided by the Ethics Committee of Shenzhen Hospital of Guangzhou University of Chinese Medicine (Futian). Data from the original CRF and biological samples will be stored for an additional 5 years after the trial ends.

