### 2.2 Study design

This study is designed as a 12-weeks, single-center, double-armed, parallel, randomized, controlled clinical trial. A total of 96 eligible participants will be recruited from Shenzhen Hospital of Guangzhou University of Chinese Medicine (Futian) and randomized in a 1:1 ratio into two groups to receive basic treatment. As a supplement to the clinical study, participants’ fasting serum and urine samples will be subjected to untargeted and targeted metabolomic assays. Liquid chromatography–mass spectrometry (LC-MS) will be used to compare metabolites before and after treatment in the experimental and control groups. Basic analysis of metabolites, multivariate statistical analysis, pathway enrichment analysis, and topological analysis of the screened differential metabolites will be performed.

All patients should have voluntarily participated and signed an informed consent form with good compliance. Informed consent will be obtained from all participants prior to enrollment. A flowchart and schedule of the clinical trial is shown in Figure 1 and Table 1, respectively. The protocol was designed according to the Standard Protocol Items: Recommendations for Interventional Trials (SPIRIT) guidelines (Chan et al., 2013) and the Declaration of Helsinki. The SPIRIT checklist is shown in Supplementary Material S2.

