### 2.11 Recruitment

Participants in this clinical trial will be recruited mainly from outpatients and inpatients of the Endocrinology Department of the Guangzhou University of Chinese Medicine Shenzhen Hospital (Futian). Patients will also be recruited through posters and publicity on social media platforms. All examinations during the trial will be free of charge to participants. Members of the project team will conduct a detailed protocol explanation and screening of patients who volunteer to participate in the trial to ensure that participants fully understand the trial process and the inclusion criteria.

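### Sealed envelopes go only to the clinicians who assign patients in an open-label trial, and Table 1 puts allocation before the day 0 baselines, so concealment is weakly protected

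*Protocol article*

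**What the plan says.** Four places in the protocol article bear on this.

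- **Section 2.9, order of events.** "Patients successfully enrolled in the study will be randomly assigned to either the treatment or control group at a 1:1 ratio". Assignment comes after enrolment.
- **Section 2.9, custody.** "The randomization sequence number will be sealed in an opaque envelope and provided only to clinicians so that the participants can be assigned". The sentence ends by saying that they are assigned to their regimen accordingly.
- **Section 2.9, masking.** "Since this trial is an open-label study, participants and physicians will be aware of the assignment protocol". Masking extends only to those who analyse the data.
- **Section 2.11, screening.** "Members of the project team will conduct a detailed protocol explanation and screening of patients who volunteer to participate in the trial". The article does not say whether these team members are the clinicians who receive the envelopes.

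Table 1 has two baseline columns, one for days -14 to 0 and one for day 0 ± 2 days. As extracted, it ticks allocation in the first, with consent and the eligibility criteria. Visceral fat area and TCM symptoms are first ticked in the second. Section 2.8.2 names these two as the primary outcomes.

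**The concern.** A sealed opaque envelope hides the next assignment as long as nobody with a stake in it can open it early, take it out of order, or decide whom to enter once it is known. The usual protection is to give the envelopes to someone with no such stake. Section 2.9 gives them to clinicians and to nobody else, in a trial where physicians know what each patient has received.

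Two kinds of bias are at stake:

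1. **Selection at entry.** If a clinician knows the next arm, a patient can be deferred or judged ineligible. Several entry criteria leave room for judgement: tongue and pulse findings and symptom counts in section 2.4, and inability to follow procedures in section 2.5. The resulting imbalance would reach every outcome, and masked analysts could not undo it.
2. **Baseline recorded with the arm known.** Both primary outcomes are changes from baseline. If allocation precedes the day 0 measurements, the starting value itself can be affected, most readily for the symptom score.

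With no placebo and no masking of patients or physicians, concealment up to the moment of assignment is one of the few protections the design has.

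**Working it through.** The plan gives no figure for concealment, so there is none to reproduce. The main check compares the texts.

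**Step 1. Is custody stated or merely omitted?** It is stated. Section 2.9 names the recipients (clinicians), excludes others (only), and gives the purpose (assigning participants). A fuller protocol could add numbering or an opening log. It could not add a holder outside the clinicians without contradicting this sentence.

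**Step 2. Which safeguards does the text give?** There are three: the envelope is sealed, it is opaque, and assignment follows successful enrolment. The first two depend on the conduct of the person holding the envelope. The third is weakened by steps 3 and 4.

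**Step 3. When is allocation done relative to baseline?**

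| Item in Table 1 | First ticked |
|---|---|
| Consent, eligibility | days -14 to 0 |
| Allocation | days -14 to 0 |
| Visceral fat area | day 0 ± 2 |
| TCM symptoms | day 0 ± 2 |

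The windows meet at day 0, so allocation on the same day as baseline is possible. The table nevertheless permits allocation up to 14 days earlier, and nothing requires the baselines to be recorded first. The consequence for a change score is direct: change = week 12 value − baseline value. If one arm's baseline is scored b points too high because the arm is known, that arm's mean change shifts by −b points, and so does the between-arm difference.

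**Step 4. Can eligibility be judged without knowing the arm?** Inclusion criterion 4 in section 2.4 applies the restriction on prior Chinese medicine to the experimental group alone. Read literally, it can only be checked once the arm is known, which conflicts with assignment after enrolment. It may be a slip of wording, but it points the same way as Table 1.

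**Step 5. Illustration of size (assumed inputs).** The documents give neither a steering rate nor a block size. Suppose a fraction f of allocations is steered so that those patients differ by 1 SD in prognosis between arms. The bias is then δ = f × 1 SD. With n = 48 per arm (section 2.10), the noncentrality is δ√(n/2), there are 94 degrees of freedom, and the two-sided 5% critical value is 1.986.

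- f = 10%: δ = 0.1, noncentrality 0.1 × √24 = 0.490, rejection probability under no true effect 0.077.
- f = 20%: δ = 0.2, noncentrality 0.2 × √24 = 0.980, rejection probability 0.163.

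With 38 per arm, the number left after the planned 20% dropout, the same biases give 0.071 and 0.138. These figures only translate an assumed bias into an error rate.

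**The case against.** The strongest reply has four parts.

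- **The safeguards are real.** Sealed opaque envelopes are a recognised concealment measure, and assignment follows enrolment. This stands. A reader might infer that clinicians control the sequence or that concealment is absent. The documents support neither: holding a sealed envelope is not generating or seeing the sequence, and nothing permits early opening.
- **The sentence may only restrict disclosure.** It can be read as telling the allocation to those who must deliver it, in contrast to the masked analysts, perhaps one envelope per enrolled patient. That reading is possible, because the text does not say whether clinicians hold the full set. It still makes the clinicians the ones who receive and act on the envelope.
- **The same people need not screen, assign and treat.** This also stands. Section 2.11 mentions only project team members, and the article neither equates nor separates the two groups. In addition, being unmasked after assignment is a matter of blinding. Knowledge of past allocations breaks concealment only if the next one can be predicted or seen.
- **An article condenses.** Numbering, opening logs and sequence generation may be in the full protocol, and their absence here is not held against the plan. The point rests on what is written: the custody rule and the position of allocation in Table 1.

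It would also be too strong to say that the analysis could never reveal steering. Many baseline variables are collected, so steering on measured factors might appear as imbalance. Steering on unmeasured factors would not.

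**Conclusion.** The point holds in limited form. Section 2.9 gives the envelopes only to clinicians, for the purpose of assigning patients in a single-centre open-label trial. It leaves no place for an independent holder, so concealment rests on the seal and is weakly protected. Table 1 allows allocation before the day 0 baselines of both primary outcomes, so those baselines may be taken with the arm known.

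This is a weakness of procedure that should be corrected. It is not evidence that allocation has been or will be subverted. Its size cannot be derived from the documents: the error rates of about 8% and 16% rest wholly on assumed steering of 10% and 20% and an assumed 1 SD difference in prognosis. The Table 1 part assumes that the extracted tick positions match the published table.

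**What to change.** 1. In section 2.9, replace the rule that envelopes go only to clinicians. Sequentially numbered sealed opaque envelopes should be held by an existing staff member with no role in screening, treatment or outcome rating, for example in data management or the dispensing pharmacy.
2. State that this person releases the next envelope in order, and only after consent, confirmed eligibility and recorded baseline measurements, including visceral fat area and the TCM score.
3. Move allocation in Table 1 so that it follows the day 0 baseline.
4. Reconcile inclusion criterion 4 with assignment after enrolment, so that eligibility can be judged without knowing the arm.

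The cost is a few lines of protocol text and one contact with the holder per patient. The documents do not describe staffing, so the sponsor must confirm that a suitable uninvolved person exists. Section 5 says the trial was already recruiting at submission, so the change protects only patients not yet randomised. For those already randomised, the report should state who held and opened the envelopes and whether baselines were recorded before assignment.

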**FIGURE 1 F1:**
[figure not shown]
Flow chart of the clinical trial.

**TABLE 1 T1:** Schedule of the clinical trial.

Project time	Screening/baseline		Treatment			
	-14–0 days	0±2 days	Visit 1 4weeks± 2days	Visit 2 6weeks± 4days	Visit 3 8weeks± 6days	Visit 4 12weeks± 7days
Eligibility screening						
Inclusion/exclusion criteria	**✓**					
Informed consent form	**✓**					
Allocation	**✓**					
General information	**✓**					
Family history	**✓**					
Medical history	**✓**					
Drinking history	**✓**					
Physical examination^a^	**✓**	**✓**	**✓**	**✓**	**✓**	**✓**
Vital signs^b^	**✓**	**✓**	**✓**	**✓**	**✓**	**✓**
Ultrasound of liver	**✓**					**✓**
bioelectrical impedance analysis						
visceral fat area		**✓**				**✓**
subcutaneous fat area		**✓**				**✓**
Electrocardiography	**✓**			**✓**		**✓**
Laboratory examination						
Routine blood test		**✓**		**✓**		**✓**
Routine urine test		**✓**		**✓**		**✓**
Fasting blood sugar		**✓**		**✓**		**✓**
2-h plasma glucose		**✓**				**✓**
Glycated hemoglobin		**✓**				**✓**
Fasting insulin		**✓**				**✓**
Blood lipids		**✓**		**✓**		**✓**
Liver function		**✓**		**✓**		**✓**
Renal function		**✓**		**✓**		**✓**
Traditional Chinese medicine symptoms		**✓**	**✓**	**✓**	**✓**	**✓**
Fibrosis 4 Score		**✓**				**✓**
Homeostasis model assessment-insulin resistance		**✓**				**✓**
homeostatic model assessment for β-cell		**✓**				**✓**
Metabolomics test^c^						
Serum sample		**✓**				**✓**
Urine sample		**✓**				**✓**
Adverse event			**✓**	**✓**	**✓**	**✓**
Prescription		**✓**	**✓**	**✓**	**✓**	**✓**
Combined drugs		**✓**	**✓**	**✓**	**✓**	**✓**
Summary of the analysis						**✓**

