#### 2.8.2 Primary outcomes

The primary outcome is change in visceral fat area (VFA) and TCM syndromes efficacy score scale. Changes in VFA will be compared between the two groups before and after treatment. The indicator will be tested at baseline and week 12. The TCM symptom scoring standard is presented in Supplementary Material S3.

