#### 2.8.3 Secondary outcomes

1) Changes in hepatic steatosis factors by ultrasound grading of steatosis.2) Changes in metabolic parameters: glycated hemoglobin (HbA1c) levels, fasting plasma glucose (FPG), 2-h plasma glucose (2h-PG), fasting insulin, blood lipids including total cholesterol (TC), triglycerides (TG), high-density lipoprotein-cholesterol (c-HDL), low-density lipoprotein (c-LDL), apolipoprotein A (ApoA), and apolipoprotein B (ApoB).3) Changes in anthropometric parameters: Waist-to-height ratio (WHtR), Body Mass Index (BMI), waist circumference (WC), hip circumference (HC).4) Changes in hepatic fibrosis factors and hepatic function: The changes in Fibrosis 4 Score (FIB-4, http://gihep.com/calculators/hepatology/fibrosis-4-score/) can be calculated by the formula:

$$\mathrm{Age}\;\left(\mathrm{years}\right)\text{x}\;\mathrm{AST}\;/\mathrm{PLT}\;\left(\times 10^{9}/L\right)\text{x}\sqrt{\mathrm{ALT}}$$

The units of measurement for ALT and AST are aligned with those for age and PLT.

Definitions for the following abbreviations: AST: Aspartate aminotransferase; PLT: platelet; ALT: Alanine aminotransferase.5) Changes in visceral fat area.

All measurements will be performed at baseline and at week 12. Additional FPG and blood lipid test will be performed at week 6.

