### 3.2 Monitoring

To maintain high-quality data and ensure the smooth running of the trial, all protocol implementers and investigators will undergo systematic and rigorous training. Patient screening, data entry, dosing, adverse event reporting, dosing records, and biospecimen extraction will be performed. The data of numbered participants will be recorded in detail on standardized CRF forms and biospecimens will be stored under the same number. Data will be recorded independently by two research assistants, updated in real time, and synchronized on the CRF form after each visit. Quality control and data review will be performed regularly by the study monitoring committee to ensure accuracy and completeness of data entry. The quality and progress of the project will be evaluated. An interim analysis of the primary outcome will be conducted to monitor efficacy and safety when 50% enrollment is reached. This is independent of the sponsor. All patient information and clinical data will be kept confidential on a professional data platform.

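### Only the analysts are masked in an open-label trial without placebo; nothing masks whoever grades ultrasound, measures circumferences or scores the TCM scale

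*Protocol article*

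**What the plan says.** Section 2.9 sets out who knows the treatment arm. It calls the trial open-label and says that "participants and physicians will be aware of the assignment protocol, whereas data analysts and statisticians will not be aware of the distribution results". No other group is mentioned, and no other section masks anyone who takes a measurement. Section 2.7 adds JTTF to conventional treatment in one arm and gives the other arm no placebo.

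The outcomes that bear on this are:

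- Section 2.8.2: "The primary outcome is change in visceral fat area (VFA) and TCM syndromes efficacy score scale". The scoring standard is in Supplementary Material S3, which is not shown. Table 1 schedules the TCM symptoms at baseline and at weeks 4, 6, 8 and 12.
- Section 2.8.3, first secondary outcome: "Changes in hepatic steatosis factors by ultrasound grading of steatosis". The same section lists waist circumference, hip circumference and waist-to-height ratio.
- Table 1 places visceral fat area under "bioelectrical impedance analysis".

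Section 3.2 describes data handling: "Data will be recorded independently by two research assistants, updated in real time, and synchronized on the CRF form after each visit". It does not say whether these assistants assess outcomes or whether they know the arm. The limitations in section 4 do not mention open-label assessment.

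**The concern.** With no placebo, bias from participants' and physicians' knowledge of the arm cannot be designed out. The place where bias can still be reduced is the measurement itself, and the stated scheme offers no protection there. An analyst who does not know which group is which will faithfully analyse values that may already lean one way.

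The outcomes at risk are not marginal. The TCM score is one of the two primary outcomes. Ultrasound grade is the only direct measure of liver fat in the outcome list, and reducing fat accumulation is the first effect named in the hypothesis of section 2.1.1. If assessors who know the arm score even slightly in favour of JTTF, that shift adds to the estimated treatment effect and cannot afterwards be told apart from it.

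**Working it through.** **Step 1. Which outcomes could an assessor's knowledge enter?**

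| Outcome | Status | Assessor named? | Masking stated? | Route for assessor bias |
|---|---|---|---|---|
| TCM score | Primary | No | No | Any item judged by a rater; patient-reported items are exposed whoever records them |
| Visceral fat area | Primary | No | No | Device reading; no operator judgement is described |
| Ultrasound steatosis grade | Secondary | No | No | The grade is a reader's judgement |
| Waist, hip, waist-to-height ratio | Secondary | No | No | Hand measurement |

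The concern therefore rests on the first, third and fourth rows.

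**Step 2. Could baseline values be affected too?** Table 1, as it reads after extraction, ticks allocation and liver ultrasound in the same screening window (days −14 to 0), and first ticks TCM symptoms at day 0±2. The schedule does not show that baseline assessments come before the arm is known. The fix should therefore cover baseline as well as week 12.

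**Step 3. Illustration of size.** The documents give no figure for assessment bias, so there is no figure of the plan's own to reproduce. Inputs:

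- n per arm: 96/2 = 48 as randomised and 76/2 = 38 as evaluable (section 2.10).
- Test: two-sample t-test at 5% (sections 2.10 and 3.1). Two-sided is assumed, because the article does not state sidedness.
- True treatment effect: zero.
- Total bias b, in SD units, shifting one arm: assumed at 0.1, 0.2 and 0.3.

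The test statistic then follows a noncentral t distribution with 2n − 2 degrees of freedom and noncentrality λ = b × √(n/2). The false-positive rate is the probability that it falls beyond the usual two-sided 5% limits.

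- n = 38: √(38/2) = 4.359, so λ = 0.44, 0.87 and 1.31.
- n = 48: √(48/2) = 4.899, so λ = 0.49, 0.98 and 1.47.

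| Assumed total bias b | 38 per arm | 48 per arm |
|---|---|---|
| 0 | 5.0% | 5.0% |
| 0.1 SD | 7.2% | 7.7% |
| 0.2 SD | 13.8% | 16.3% |
| 0.3 SD | 25.2% | 30.7% |

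**Step 4. What the figures do and do not show.** For the TCM score, b is the sum of a part from participants' own reports and a part from the assessor. Masking the assessor removes only the second. If b were 0.3 SD and the assessor's part 0.1 SD, 0.2 SD would remain and the rate would fall from 25–31% to 14–16%. If the assessor's part were 0.2 SD, 0.1 SD would remain and the rate would fall to 7–8%. The split is not known. The model also does not apply to ultrasound grade, which is ordinal and which section 3.1 assigns to a rank test or CMH test.

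**The case against.** The strongest reply is that this rests on silence. The article does not say that assessors know the arm. It does not say who they are, and a condensed article may leave such operational detail to the full protocol. That is correct as far as it goes: a reader might infer that the sonographers or scorers are unmasked, and the documents do not support that. They support only that these people may know the arm. But section 2.9 does not leave masking unaddressed. It sets out a scheme, and the scheme stops at the analysis.

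Four further limits stand.

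- A reader might extend the point to visceral fat area. That is a device reading, and no operator influence is described, so the point is not made for it.
- A reader might assume that tongue and pulse are scored TCM items. Section 2.4 lists them as diagnostic criteria. The scoring sheet is not shown, and most of the symptoms in section 2.4 are ones that a patient would report.
- A reader might take the two research assistants in section 3.2 as ready-made masked raters. Nothing says that they assess outcomes or stand apart from allocation. Section 3.2 also lists dosing records among the trial tasks, and Table 1 schedules prescriptions and combined drugs at follow-up, so staff completing the CRF could well see the arm.
- The documents do not describe staffing, so it cannot be said that masking would be free.

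**Conclusion.** The point holds in this form: the stated scheme masks only the analysis, and ultrasound grade, circumferences and any rater-judged part of the TCM score may be assessed with the arm known. Masking the analysts cannot remove bias that enters there. This is a design choice that should be changed. It is not an internal contradiction.

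Its size cannot be derived from the documents. The range of about 14–16% false positives at 0.2 SD and 25–31% at 0.3 SD is an illustration for a continuous score, under an assumed total bias, a zero true effect and a two-sided 5% t-test with 38 to 48 per arm. A reader might take it as the error that masking assessors would remove. It is not, because participants know their arm and their own symptom reports stay exposed.

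The case is clearest for ultrasound grade and circumferences, which involve no self-report and can in principle be fully masked. For the TCM score the gain is partial, and its extent depends on the unseen scoring sheet.

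**What to change.** Amend section 2.9 as follows.

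1. State that ultrasound requests do not show the arm, and that baseline and week-12 scans are graded without sight of allocation.
2. Where existing staff allow, have circumferences and any rater-judged TCM items taken by someone not involved in allocation, prescribing or dosing records.
3. In section 4, state as a limitation that participants know their arm and that patient-reported TCM items therefore remain unmasked.

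Sample size, alpha, power, outcomes and visits do not change. The cost is a small logistical change in request forms and in who takes which measurement. Masking will be imperfect, since participants may reveal their treatment. Section 5 says that recruitment was already under way, so the report should also state which assessments were made before the change.

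If the full protocol already masks these assessors, one sentence in section 2.9 saying so is enough for items 1 and 2.
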